### Design

The SMART-Therapy trial is designed as a randomised, controlled, assessor-blinded superiority trial, with two parallel groups, using a 1:1 allocation ratio. The two groups both receive eight sessions with a mental health worker in addition to their routine care during a three month window, with one group being delivered the recovery intervention, and the other being delivered a befriending intervention as a comparison condition. Outcome measures are completed at baseline (prior to randomisation) and are repeated at 3, 6 and 9 months following baseline.

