### Participants

The study is being conducted across multiple public community mental health services in the state of Victoria, Australia, including clinical mental health services, and not-for-profit organisation-run community mental health support services. Potential participants are identified via referral from practitioners in collaborating services, supplemented by review of case-lists, plus advertising within services, and in print and online social media.

Inclusion criteria are: (a) age between 18 and 65 years inclusive; (b) diagnosis of a nonorganic psychotic disorder (schizophrenia-related disorder or bipolar disorder or major depressive disorder with psychotic features present within the past 2 years), confirmed using the Structured Clinical Interview for DSM-IV-TR Axis I Disorders (SCID) [49]; (c) sufficient conversational English for meaningful participation; (d) overall intellectual functioning within normal limits (having an IQ greater than 70, as estimated by the Wechsler Test of Adult Reading (WTAR) [50]) to ensure they have the cognitive capacity to provide consent, in addition to being able to adequately engage with the intervention. Exclusion criteria are: (e) initiation of a new antipsychotic medication, or commencement or completion of a formal psychological treatment, within the previous 8 weeks; (f) inpatient admission within the previous 8 weeks.

The recruitment target is 148 participants, providing 80 % power to detect medium effect sizes (*d* = 0.5) at α = .05 with 15 % attrition. This was based on an average effect size of *d* = 0.53 observed in a meta-analysis of online interventions [51].

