### Allocation and blinding

The trial uses minimisation randomisation, conducted using the software Minimpy (http://sourceforge.net/projects/minimpy). This generates random allocations based on the stratification parameters for each participant enrolled in the study. The randomisation procedure and setup of the Minimpy parameters was prepared by the study statistician to stratify by type of mental health service the person receives (clinical vs community sector vs both), symptom severity (Positive and Negative Syndrome Scale (PANSS) total ≥ vs < 67), and frequency of Internet use (daily vs less than daily). Following commencement of the trial, the software is operated by a person independent of the research team, who receives participant codes from the research team as each baseline assessment is completed, runs the allocation, and advises of allocations via return email.

Research staff conducting assessments are blind to participant allocation throughout the study. Participants are unavoidably aware of the conditions they have been randomised to. To reduce expectancy effects for superiority of the intervention over the control condition, the trial was framed as a comparison between two ways of integrating technology into mental health service delivery, with a *health* condition using technology to discuss mental health recovery, and a *social* condition using technology to support discussion about the person’s interests. To maintain assessor blinding, participants are regularly reminded not to divulge their allocated condition or any details of their intervention to assessment staff, as are their mental health workers. Breaches in blindness are recorded and addressed by changing the rater whenever possible. Blindness is also assessed at each assessment following the intervention by asking raters to nominate a guessed treatment condition for the participant and to indicate their level of confidence. The principal investigator (NT) and project manager (FF) are not blinded, and respond to any clinical and research issues during the trial that require knowledge of a participant’s’ condition.

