### Data analysis

Data are initially recorded on paper forms which are securely stored and extracted into password protected electronic files. Data extraction is conducted by research staff blind to participant allocation. Procedures to identify potential errors include double entry from selected paper files, range checks, and examination of outliers.

The primary focus of the analysis is differential changes in the SMART group versus Befriending over the full post intervention period. Analyses will be undertaken using mixed-model repeated measures (MMRM) allowing for autoregressive dependence. MMRM is well-suited to ITT analyses because this approach uses all available information from subjects. Participants with incomplete data are not discarded and missing data are not replaced with estimated values or observations carried forward. Instead maximum-likelihood estimation is applied with the available data. Where there are significant group x time interactions, planned contrasts will compare changes from baseline under each intervention.

Where outcome measures exhibit non-normal distributions across time points, appropriate transformations will be applied. If any of the outcome measures show significant baseline differences between SMART and Befriending, and between completers and noncompleters, corrections for sample imbalance and attrition bias will be applied using propensity scoring. This will involve firstly constructing a logistic regression model with treatment condition as the outcome, and baseline clinical variables and demographics as predictors, plus a “missing-at-post-therapy” variable to index differential effects of attrition. Secondly the effects of any imbalance or attrition will be addressed by including the estimated probabilities from this model (propensity scores) as a covariate in analyses.

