The differential effects on outcomes of the process variables (self-efficacy and self-stigma) and medication changes will be tested across conditions with a maximum likelihood Hierarchical Linear Modelling analysis. In these models time will be treated as a linear covariate. Baseline measures for cognitive function, recovery style, intervention engagement, diagnosis, demographics, baseline internet use and expectancy will be used as covariates, while testing interaction effects for condition and the baseline social engagement moderators (loneliness, attachment, peer group identification and peer contact). Structural equation modelling will then be used to demonstrate the mediation mechanism of outcome improvement for each condition separately, with bootstrap analyses used to obtain 95 % confidence intervals for all effect sizes.

Data will also be used as part of a broader economic evaluation of the use of the website involving cost-consequences analyses whereby incremental costs of interventions using the site are compared with the full spectrum of outcomes measured vs relevant comparators. For this study, QALYs will be calculated from AQoL8D data, and costs will be derived from estimates of the costs involved in running the website (website development and maintenance costs, forum moderation, and therapist activity data), adjusted for any differences in resource use between conditions. Standardised economic evaluation techniques will be used including incremental analysis of mean differences, with confidence intervals derived using bootstrapping.

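### The primary MMRM as described names none of the three minimisation factors and adjusts only when baseline tests are significant; prespecifying the factors would recover a small amount of power at almost no cost

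*Protocol article*

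**What the plan says.** The Allocation and blinding section states that "The trial uses minimisation randomisation, conducted using the software Minimpy". The statistician set it up "to stratify by type of mental health service the person receives (clinical vs community sector vs both), symptom severity" (PANSS total split at 67) and frequency of Internet use (daily or less than daily). That is one three-level factor and two two-level factors.

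The Data analysis section gives the primary method: "Analyses will be undertaken using mixed-model repeated measures (MMRM) allowing for autoregressive dependence". The target is the difference between arms in change over the period after the intervention. It is tested as group by time, followed by contrasts of change from baseline. The description names no minimisation factor. It does contain one covariate rule. If outcome measures differ significantly at baseline, between arms and between completers and noncompleters, a propensity score built from baseline clinical variables, demographics and a missingness indicator is added to the model.

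The planned size is given under Participants: "The recruitment target is 148 participants", "providing 80 % power to detect medium effect sizes" (d = 0.5) "at α = .05 with 15 % attrition".

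**The concern.** Minimisation makes the arms more alike on its factors than simple randomisation would. If those factors predict the quantity analysed, the treatment estimate varies less from trial to trial than a model without them assumes. The reported standard error is then too large, the interval too wide and the test conservative. The precision that the allocation bought is not collected.

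The stated covariate rule does not close this gap. It is triggered by significant differences on outcome measures, not by the allocation design. For PANSS, which is both a minimisation factor and an outcome, minimisation makes the trigger less likely to fire. So the one adjustment that the article describes depends on the data, while the variables that shaped the allocation are not named.

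At stake is a modest amount of power in a trial planned at 80% with no margin. A false-positive result is not made more likely.

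**Working it through.** **1. The plan's own figure.** Inputs from Participants and Design: d = 0.5 with SD 1, alpha 0.05 (two-sided assumed, since sidedness is not stated), power 80%, 15% attrition, 1:1 allocation.

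- Per arm: n = 2(1.960 + 0.842)² / 0.5² = 62.8, so 63 per arm and 126 in total.
- Inflated for attrition: 126 / 0.85 = 148.2. The stated 148 is reproduced.
- Evaluable per arm: 148 × 0.85 / 2 = 62.9. Noncentrality 0.5 × √(62.9/2) = 2.804. Power Φ(2.804 − 1.960) = 80.1%.

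**2. Upper limit on the effect of leaving the factors out.** Let R² be the share of the variance of the analysed quantity that the factors explain, and suppose that minimisation balances them perfectly. Let s = √(1 − R²). Then:

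- size without factors = 2[1 − Φ(1.960/s)]
- power without factors = Φ((2.804 − 1.960)/s)
- power with factors = Φ(2.804/s − 1.960)

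Example, R² = 0.10: s = 0.949; size = 2[1 − Φ(2.066)] = 3.9%; power Φ(0.890) = 81.3% without and Φ(0.996) = 84.0% with.

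| R² | Size without factors | Power without / with |
|---|---|---|
| 0 | 5.0% | 80.1 / 80.1% |
| 2% | 4.8% | 80.3 / 80.9% |
| 5% | 4.4% | 80.7 / 82.0% |
| 10% | 3.9% | 81.3 / 84.0% |

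**3. Which R² applies.** The test concerns change. Write a participant's QPR as a level effect a of the factors, the same at every visit, plus a part that varies by visit. In follow-up minus baseline, a − a = 0. Only the factors' prediction of *change* in QPR counts. The article gives no figure for it, so R² is an assumption throughout.

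**4. Simulation of change scores.** 148 participants were allocated by minimisation, 15% were lost, and the analysis was run with and without the factors. Balance is now imperfect, as it would be in practice.

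| Share of change explained | Size without factors | Power without / with | Difference |
|---|---|---|---|
| 0% | 5.0% | 79.5 / 79.3% | −0.2 |
| 3% | 4.8% | 80.2 / 80.6% | 0.4 |
| 5% | 4.4% | 81.1 / 82.3% | 1.2 |
| 10% | 4.3% | 80.7 / 83.4% | 2.7 |

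**5. Simulation of the repeated-measures test.** Four visits, autoregressive correlation 0.7, 15% monotone dropout, 2,500 runs per scenario. The correlation, factor frequencies and biased coin are assumptions. The error is about 0.4 points on size and 1 point on power.

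- Without the factors, size was 4.7 to 6.2% for group by time and 4.4 to 5.2% for mean change from baseline. Both are near nominal.
- At an assumed effect of 0.33 SD, with the factors explaining 10% of level and 5% of change, power without factors and with factor-by-visit terms was 55.3 and 56.5% (group by time), and 60.4 and 62.2% (mean change).
- Size near 3%, with a loss of roughly 8 to 11 points of power, appeared only when arms were compared on post-baseline level without using baseline. The Data analysis section does not describe that comparison.

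**The case against.** The strongest objection is that silence is not exclusion. The text is a condensed article, and the fixed-effects list of an MMRM is commonly left to an analysis plan, which is not shown here. This stands: nobody can say from this article that the factors will be left out. It does not dispose of the point, because the article does state a covariate rule for its outcome models, and that rule follows baseline significance tests and not the allocation. If the full plan already has the factors, the published description only needs to be brought into line.

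The second objection is that the consequence is conditional and conservative. This also stands. A reader might infer that the test runs well below 5% and that the trial falls short of its planned power. The document does not support either inference. The test is of change, constant effects on level cancel, and power without the factors stays at about 80%. What is lost is a gain that could have been had.

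A reader might also want the process and mediation models to match the allocation, since the article says of them "Baseline measures for cognitive function, recovery style, intervention engagement, diagnosis, demographics, baseline internet use and expectancy will be used as covariates" and so lists Internet use but neither PANSS severity nor service type. Those models do not carry the primary treatment comparison and need not change on this ground.

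Finally, it may be argued that adjusting for severity and service type would make the missing-at-random assumption more plausible. That depends on whether they predict missed visits, on which the article gives nothing, so it adds no weight here.

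**Conclusion.** The point holds as a small improvement that costs almost nothing; it is not an error that threatens the trial. The primary MMRM as described does not name the factors used in minimisation, and its only stated adjustment is triggered by the data.

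If the factors explain 3 to 10% of the variance of change in QPR, size without them is about 4.8 to 4.3% and the power forgone is about 0.5 to 3 points. If they affect only a constant level, nothing is lost. On the plan's own assumptions (d = 0.5, 15% attrition) the 80% target is met either way; the 79.5% in the simulation with no prediction of change lies within about 1 point of it. These sizes rest on assumed R² values. Only the direction, towards conservatism, is secure. Severity: minor.

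**What to change.** State in the Data analysis section that the MMRMs for the primary and secondary outcomes include service type, PANSS severity and frequency of Internet use as prespecified covariates, each with a visit interaction, whatever the result of baseline significance tests. Baseline PANSS total may enter as a continuous variable. For PANSS outcomes, the baseline value already serves this purpose.

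The visit interactions are needed: with baseline as one of the responses and complete data, a factor main effect alone cancels out of the contrasts of change.

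The cost is one sentence and about four degrees of freedom per visit (two for service type, one each for PANSS and Internet use). All three variables are known for every participant at allocation, so no extra data collection is needed.

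### The test-triggered propensity step, with a post-randomisation missingness indicator in the score, cannot correct attrition bias and, depending on how the score enters the model, can add bias

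*Protocol article*

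**What the plan says.** All of the rule stands in the Data analysis section of the protocol article.

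- **Target.** "The primary focus of the analysis is differential changes in the SMART group versus Befriending over the full post intervention period". Where the group x time interaction is significant, "planned contrasts will compare changes from baseline under each intervention".
- **Missing data.** The repeated-measures model keeps every participant and imputes nothing. "Instead maximum-likelihood estimation is applied with the available data".
- **Trigger for the extra step.** "If any of the outcome measures show significant baseline differences between SMART and Befriending, and between completers and noncompleters". No test level is given.
- **The score.** A logistic regression has treatment condition as its outcome. The predictors are baseline clinical variables and demographics, "plus a “missing-at-post-therapy” variable to index differential effects of attrition".
- **Its use.** Imbalance or attrition is then dealt with by "including the estimated probabilities from this model (propensity scores) as a covariate in analyses".

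The section does not say whether the score enters as a main effect only or also with a time interaction, nor whether the baseline score is a response or a covariate. Under Measures, a 3-month assessment that cannot be done within 6 weeks counts as missed, and the participant is seen again at the next time point. A participant flagged as missing at post-therapy can therefore still supply 6- and 9-month outcomes.

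**The concern.** Three features of the rule are at issue.

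1. **A post-randomisation variable is in the score.** Missing the 3-month visit happens after allocation. It can depend on the arm and on how the participant is doing. Adjusting the treatment comparison for a score that contains it may condition on a consequence of treatment.
2. **The wrong probability is modelled.** Attrition bias arises because some people are more likely to be observed than others. The logistic model describes arm, not observation, so its fitted values carry no correction for selective observation.
3. **Significance tests switch it on.** After correct randomisation, arm differences at baseline are due to chance. A chance difference on any outcome measure, including a secondary one, can help decide which model is used for the primary outcome.

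At stake are a primary analysis that is not fixed in advance and, for some forms of the model, a biased treatment estimate.

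**Working it through.** **Step 1. The plan's own figure.** Participants section: "providing 80 % power to detect medium effect sizes (*d* = 0.5) at α = .05 with 15 % attrition". Design section: "using a 1:1 allocation ratio". With two-sided alpha assumed, n per arm = 2(1.960 + 0.842)² / 0.5² = 62.8, so 63 per arm and 126 in total. Then 126 / 0.85 = 148.2, which agrees with the stated 148 apart from rounding. The normal approximation at 148 x 0.85 = 125.8 completers gives power 0.801. The sample size is not in question; d = 0.5 and 15% attrition serve as reference values below.

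**Step 2. How often chance trips the arm test.** Eight scales are both outcome measures and scheduled at baseline: QPR, Schizophrenia Hope Scale, UCLA Loneliness, PANSS, SEPS, DASS-21, AQoL-8D and STAR. The test level is assumed to be 0.05.

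- Independent measures: 1 - 0.95⁸ = 0.337, about 34%.
- Pairwise correlation 0.5 (assumed): about 25%.

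These rates cover the arm condition alone. Read literally, the sentence also requires a completer difference. If that test is null and independent of the arm test:

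- any measure may fail each test: 0.337² = 0.11 under independence, 0.25² = 0.06 at correlation 0.5;
- the same measure must fail both: 1 - (1 - 0.05²)⁸ = 1 - 0.9975⁸ = 0.02.

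Genuine completer differences would raise these joint figures towards the arm-only rates.

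**Step 3. The score as a main effect, with baseline in the response.** Write the mean for participant i at visit t as β_t + δ_t·arm_i + γ·s_i, with s_i the score. In the change from baseline, γ·s_i − γ·s_i = 0, so the mean change is (β_t − β_0) + (δ_t − δ_0)·arm_i. The score drops out of the group x time contrast. In simulation with missing data the estimate moved by at most about 0.005 SD.

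**Step 4. The score where it can act.** Simulation: 500 trials per scenario, N = 148, four visits, maximum likelihood with autoregressive dependence. The effect sizes and missingness mechanisms are assumptions, not trial figures. The Monte Carlo standard error of each mean is 0.005 to 0.007 SD. Entries are bias in SD units.

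| Assumed scenario | Missing at 3 months, control vs SMART | Baseline as covariate, no score | Same, with planned score | Score x time, baseline in response |
|---|---|---|---|---|
| Arm and unmeasured prognosis drive missingness; all return; true effect 0 | 19% vs 36% | +0.010 | +0.084 | +0.084 |
| Second informative mechanism; all return; true effect 0 | 13% vs 30% | +0.006 | +0.051 | +0.054 |
| Poor 3-month response drives missingness; all return; true effect 0.5 | 24% vs 16% | -0.014 | -0.053 | -0.053 |
| First mechanism; none return; true effect 0 | 19% vs 36% | +0.068 | +0.069 | +0.069 |
| Second mechanism; none return; true effect 0 | 12% vs 30% | +0.125 | +0.126 | +0.128 |
| Completely at random; none return; true effect 0 | 15% vs 15% | 0.000 | -0.001 | -0.001 |

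Under the first mechanism, with half or all of those missing at 3 months returning, bias with the planned score was +0.07 to +0.08 SD. In its first row, a score built from baseline variables only gave +0.011 SD with baseline as a covariate, so the added bias comes from the indicator. Type I error in that row was 0.122 with the planned score and 0.062 without it (baseline as covariate).

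**Reading.** Where participants return, the score adds bias. Where they do not, the attrition bias is the same with and without it. Under missingness completely at random it does nothing.

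**The case against.** The best defence is that the text, taken plainly, enters the score as a covariate and contrasts changes from baseline. On that reading the score is nearly inert (Step 3), and no bias results. This stands: the protocol does not state the model form under which the bias appears. But an inert score also makes no correction to the change contrast, so this reading does not rescue the step.

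The bias figures depend on assumed mechanisms, several with more than the planned 15% attrition, and on participants returning after a missed visit. This also stands. A reader might infer that the primary estimate will be biased; the documents support only that it can be.

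A reader might count totals together with their subscales, reach 17 scores, and infer a trigger rate of 1 - 0.95¹⁷ = 58%. The documents do not support that. They speak of outcome measures, a total is not independent of its own subscales, PANSS total is constrained by the minimisation, and the sentence joins the arm condition to a completer condition.

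A reader might also infer that the step serves no purpose at all. That goes too far. Its baseline predictors can adjust for chance imbalance in a model of post-baseline scores with baseline as a covariate. Covariates named in advance would do the same without the test or the indicator.

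**Conclusion.** The concern holds in limited form, as a should-fix.

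- **Certain from the text.** A variable arising after randomisation is in the score, arm is what the score models, and significance tests decide whether it is used. The score therefore cannot correct attrition bias.
- **Conditional.** Added bias needs missingness related to arm and prognosis (or to response, where treatment has an effect), participants returning after a missed 3-month visit, and a score that acts on post-baseline differences. Under those assumptions it was about +0.07 to +0.08 SD against about +0.01 SD without the score, roughly 15% of the planned d = 0.5 (0.075 / 0.5). A second informative mechanism gave about +0.05 SD. With missingness at random in both arms the score added none.
- **Model choice by chance.** The arm condition is met by chance with probability about 25% to 34% for eight measures at the 0.05 level. The probability is lower if a completer difference must also be significant, as the sentence literally says.

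The recruitment target of 148 is unaffected.

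**What to change.** Delete the test-triggered propensity step, and take the missing-at-post-therapy variable out of any adjustment of the treatment comparison. Instead, in every analysis and whatever the baseline comparison shows, adjust for baseline covariates named in advance. These should include the three minimisation factors (service type, PANSS total at the 67 cut-point, frequency of Internet use) and any baseline variables expected to predict dropout. Where the contrast is group x time, give these covariates time interactions; otherwise they drop out of the change contrast just as the score does. Rely on the maximum-likelihood model already stated for missing data, and examine attrition in a sensitivity analysis, whose form can be left to the analysis plan. Whether baseline stays in the response or becomes a covariate is a separate choice that this point does not require.

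The cost is a change of wording and the loss of an ad hoc adjustment. No new data are needed.

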### Befriending

Participants in the comparison condition receive sessions based upon a neutral social contact, involving shared activity and discussion about non-mental health topics such as current affairs, recent events and activities in the participant’s life, and the participant’s interests. This is a manualised intervention, the structure of which is based upon the befriending protocol of Bendall et al. [52], a credible and acceptable comparison condition [53], which has been used as a control condition to match for therapist time in a number of psychosocial intervention trials [54–56]. In this trial the standard protocol is augmented by use of the tablet computer to browse Internet sites related to participants’ interests, and as a potential means of facilitating discussion. This comparison condition was selected to provide a control for both therapist time, and for engagement in the use of technology.

In both groups, interventions are continued until, (a) all eight sessions are completed, (b) the end of the three month therapy delivery window is reached, or (c) the participant chooses to withdraw. If participants experience significant distress or deterioration in their mental state, researchers remind participants of their right to withdraw, and encourage them to make an informed choice about their ongoing participation. If participants wish to discontinue intervention sessions, they are still followed up for assessment if willing to do so.

Participant adherence to protocols will be monitored through records of session attendance. In secondary analyses, attendance of at least four sessions will be considered as the threshold for receiving a minimum dose of the intervention. Workers attend weekly supervision led by NT to ensure protocol fidelity. Worker fidelity will be further assessed by a researcher blind to participant allocation listening to a random sample of audio recordings of sessions, and being asked to allocate sessions to condition.

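### A single straight line for time in the process-variable and medication models can create false process–outcome associations if both bend when sessions end at 3 months

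*Protocol article*

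**What the plan says.** The Data analysis section describes a hierarchical linear model separate from the primary analysis. Its purpose is given as: "The differential effects on outcomes of the process variables (self-efficacy and self-stigma) and medication changes will be tested across conditions". The coding of time is fixed in one sentence: "In these models time will be treated as a linear covariate". No quadratic, piecewise or categorical alternative is mentioned for these models. The interactions listed are between condition and baseline moderators ("while testing interaction effects for condition and the baseline social engagement moderators"); no condition × time term is listed.

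The Design section says that both groups receive their eight sessions "in addition to their routine care during a three month window", and that outcome measures "are repeated at 3, 6 and 9 months following baseline". The Befriending section, for both groups, ends sessions at the latest when "the end of the three month therapy delivery window is reached". Table 1 marks both interventions only in weeks 1–12, and schedules the QPR, the self-stigma scale and the self-efficacy measures at baseline and at all three follow-ups.

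The primary mixed model is described differently: "Where there are significant group x time interactions, planned contrasts will compare changes from baseline under each intervention". No linear restriction on time is stated there.

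**The concern.** The schedule has one interval with sessions and two without. A single slope assumes the same rate of change in all three. If scores move during the sessions and then level off or fall back, the line is too high at baseline, too low at 3 months and wrong again at 9 months.

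One badly fitted curve mainly adds noise. Here the model relates two variables that may share a time course. The part of the bend that the line misses stays in both the process variable and the outcome, with the same sign at the same visits. The process coefficient absorbs it, even when a person's own changes in self-stigma or self-efficacy have nothing to do with that person's changes in recovery.

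At stake is a named secondary aim: whether the intervention works through self-stigma and self-efficacy. The likely error is to report a process–outcome link when both measures merely moved over the same months.

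**Working it through.** **Inputs.** From the protocol: 148 recruited, 15% attrition, d = 0.5, 1:1 allocation, visits at 0, 3, 6 and 9 months. The target reproduces: 2 × (1.96 + 0.84)² / 0.5² = 62.7, so 63 per arm, and 126 / 0.85 = 148.2. I use n = 126 completers.

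Assumed, because the protocol does not give them:
- between-visit correlation r = 0.5 to 0.7, exchangeable;
- process variable entered as its value at each visit;
- baseline on the time axis;
- two-sided 5% test;
- curve shapes as below, the same for process and outcome;
- no within-person link beyond the shared curve.

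**Step 1: what the line misses.** Fit a straight line to each unit curve at the four visits.
- Step (0, 1, 1, 1): fitted 0.3, 0.6, 0.9, 1.2; residuals −0.3, 0.4, 0.1, −0.2; sum of squares S = 0.30.
- Full fade (0, 1, 0.5, 0): fitted 0.45, 0.40, 0.35, 0.30; residuals −0.45, 0.60, 0.15, −0.30; S = 0.675.
- Linear course: S = 0.

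**Step 2: from misfit to false positives.** Let D be the average misfit sum of squares per participant. With a height of 0.5 SD, D = 0.25 × S if both arms follow the curve. If only SMART does, and the model lets the slope differ by arm, D = 0.125 × S. Within-person noise contributes 3(1 − r). Then, approximately,

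b = D / [3(1 − r) + D], z = b × √(3n) = b × 19.44, rate = Φ(z − 1.96) + Φ(−z − 1.96).

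| Curve (0.5 SD) | D | z at r = 0.5 / 0.7 | Rate at r = 0.5 / 0.7 |
|---|---|---|---|
| Step, SMART only | 0.0375 | 0.47 / 0.78 | 7.6% / 12.2% |
| Step, both arms | 0.075 | 0.93 / 1.50 | 15% / 32% |
| Full fade, SMART only | 0.084 | 1.04 / 1.67 | 18% / 38% |
| Full fade, both arms | 0.169 | 1.97 / 3.07 | 50% / 87% |
| Linear | 0 | 0 / 0 | 5% / 5% |

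Example, step in both arms at r = 0.5: b = 0.075 / 1.575 = 0.0476; z = 0.0476 × 19.44 = 0.93; rate 15%.

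Simulation of the same settings gives 7–12%, 15–31%, 18–38% and 51–88% for the first four rows. Categorical visit with condition × visit gives about 5% throughout. A random-intercept fit gives 7–11% and 15–34% for the two SMART-only rows.

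**Step 3: is the interaction needed?** Take the SMART-only step with no condition × time term. Each arm then departs from the pooled curve by 0.25 SD. The step's sum of squares about its own mean is 0.75.
- Linear time alone: D = 0.0625 × (0.75 + 0.30) = 0.0656; z = 0.81 / 1.32; rate 13% / 26%.
- Categorical visit alone: D = 0.0625 × 0.75 = 0.0469; z = 0.59 / 0.96; rate 9% / 16%.

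So categorical visit without its interaction with condition removes only part of the inflation. The SMART-only rows in the table already give the plan the benefit of a slope by arm that it does not list.

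**The case against.** **The bend is assumed.** Nothing in the protocol predicts a step or a fade. Workers encourage independent use of the site, which has a forum and self-monitoring tools, and engagement is recorded up to 9 months, so gradual change is possible. This stands: if change is linear there is no misfit, and a slope is the more efficient description. The answer is that four visits allow the shape to be estimated, so it need not be fixed in advance.

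**The size depends on the scenario.** The larger rates need both arms to move, or the effect to fade. The design effect is a 0.5 SD difference between arms, and a SMART-only step of that size gives 7–12%. A shared step of only 0.3 SD gives about 5–8%. This also stands, so the result is a range and not one headline figure.

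**Baseline may not be on the time axis.** The text does not say. If only 3 to 9 months were modelled, the step would be flat and the steady fade straight, and the problem would go. Measures repeated from baseline make the four-visit reading the natural one, but it is a reading.

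**Stronger inferences that the document does not support.** A reader might infer that linear time makes the trial miss fading treatment effects. These models list no condition × time test; such effects belong to the primary mixed model. A reader might also infer that the moderator tests are damaged. With time as a main-effect covariate, its coding hardly touches a condition × moderator term: in a simulated half-fading, moderated effect, power was 63% under either coding. Nor is the mediation claim shown to rest on linear time. Structural equation modelling follows as a separate step, and its time coding is not stated.

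**Conclusion.** The point holds conditionally. The protocol fixes a straight line where its own schedule makes a bend at 3 months plausible. If process variable and outcome share that bend, a nominal 5% test of the process coefficient runs at about 7–12% in the mildest case examined above 0.3 SD (a 0.5 SD step in SMART only) and up to 51–88% in the worst (a full fade in both arms). Categorical visit with condition × visit holds about 5%. These figures rest on the assumed curves, r = 0.5 to 0.7, 126 participants, process variables entered visit by visit, and baseline on the time axis. The same reasoning covers the medication term only if doses also shift at 3 months.

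Only secondary process and medication models are affected. The primary QPR comparison and the recruitment target stand. This is a worthwhile, inexpensive improvement and not a threat to the trial's main conclusion.

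**What to change.** In the process-variable and medication models, replace linear time with visit as a categorical factor, or with a piecewise slope with a knot at 3 months, and include its interaction with condition. State whether baseline is one of the modelled visits. Make the change before unblinded analysis.

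Cost: categorical visit with its interaction uses six time parameters, against two for a slope by arm or one for a common slope. That is four or five more, with about 3 × 126 = 378 within-person degrees of freedom available. No new data are needed. The downside is some loss of efficiency for time effects if the true course is linear; the piecewise version, with four time parameters, loses less.
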